Study 2012-001863-64 was a proof of concept study in male and female intensive care patients (*N* = 40; 1:1) that investigated the clinical effect of repeated orally inhaled doses of solnatide on alveolar liquid clearance in acute lung injury. For safety reasons and according to effective pharmacological doses observed in various animal models, the second highest dose of the Phase I clinical study was chosen: 125 mg solnatide (nebulizer filling dose) twice daily (i.e., every 12 h) delivered per endotracheal inhalation to each subject. The main efficacy outcome was a positive trend in pulmonary edema (EVLWI) reduction in the whole study population, which is significant and more pronounced in patients with an initial Sequential Organ Failure Assessment (SOFA) score above 10 inhaling solnatide versus placebo (*P* = 0.04; exploratory subgroup analysis). The secondary endpoint analysis revealed a trend towards an earlier improvement of peak, plateau and mean airway pressure, PEEP, and Murray lung injury score in patients treated with solnatide. This effect was again most prominent in patients with an initial SOFA score > 10 (exploratory subgroup analysis). In addition, a shorter duration of mechanical ventilation and increased number of ventilator-free days in patients receiving solnatide inhalations versus placebo was observed, which again was more pronounced in patients with initial SOFA score above 10 (*P* = 0.06; exploratory subgroup analysis). No significant differences in the occurrence of adverse events and severe adverse events were found between the study groups that could not be explained by the underlying diseases [23].

Study 2013-000716-21 was a pilot study that investigated the clinical effect of orally inhaled solnatide on treatment of primary graft dysfunction (PGD) in mechanically ventilated patients (*N* = 20; 1:1) after primary lung transplantation. When compared to placebo, oral inhalation of solnatide in patients with PGD following lung transplantation led to earlier improvement of gas exchange, reduction of EVLWI, earlier extubation / shorter mechanical ventilation, a shorter stay at the ICU, and earlier discharge from the hospital. No drug-related adverse events, drug-related serious adverse events, or deaths were reported.

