### Sample size {14}

Given that the primary objective of the study is to investigate the safety of solnatide, the study sample size of 95 randomized patients is based on feasibility criteria.

Patients will be randomized to 3 groups of 20 patients each, representing the 3 multiple ascending dose groups receiving solnatide at doses of 5 mg, 60 mg and 125 mg, and 35 patients will receiving placebo in total, with 15 patients receiving placebo in Dosing Group A (low dose) and Dosing Group B (middle dose) and 20 patients receiving placebo in Dosing Group C (high dose).

Nevertheless, considering the key preliminary efficacy endpoint and the results of a Phase IIa study (2012-001863-64), a sample size of 20 evaluable patients in each treatment group will have approximately 80% power to detect a difference in means between solnatide and placebo of 3.2 ml/kg in the change from baseline to day 7 of EVLWI with a common SD of 3.5 using a two-group *t*-test with a 0.05 two-sided significance level and no alpha level adjustment for multiple testing.

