## Assignment of interventions: allocation

### Sequence generation {16a}, concealment mechanism {16b} and implementation {16c}

A randomization plan will be generated before study start. No stratification factors are planned. Three different randomization lists (one for each step of the study) will be prepared with the following randomization ratios:
2:1 in the first step of solnatide 5 mg vs. placebo4:1 in the second step of solnatide 60 mg vs. placebo4:1 in the third step of solnatide 125 mg vs. placebo

The randomization process will be managed electronically (block-wise generation of random numbers) by means of an Interactive Web Response System (IWRS) to ensure that treatment assignment is unbiased and concealed from patients and investigator staff. The results of the randomization are merely revealed to the responsible study pharmacist, who will then facilitate the preparation of the respective IMP. IMP vials are transferred to the investigators in a neutral container. Solnatide and placebo solutions cannot be distinguished from one another by the investigators.

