#### Sequential Organ Failure Assessment (SOFA)

The absolute value and the change from baseline will be analyzed for SOFA score by means of summary descriptive statistics at each time point until day 7.

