#### Spontaneous Breathing Trial

The time (in days) from the first spontaneous breathing trial to the first successful extubation / unassisted breathing will be calculated. Summary descriptive statistics will be provided.

In addition, patients will be classified according to the following outcome definitions [32]:
SimpleSuccessful SBT after the first attemptDifficultFailed SBT at first attempt andRequired up to three trials orRequired < 7 days to reach successful SBTProlongedRequired > 7 days to reach successful SBT

#### Time to extubation through day 28

Time to extubation (in days) is defined as the difference between the first extubation date and the randomization date. Patients still intubated at day 28 or who die while still intubated will be censored at day 28. Summary descriptive statistics will be provided for the time to extubation.

#### Ventilator-free days (VFD) through day 28

VFD is defined as the number of days from randomization to day 28 after achieving unassisted breathing for patients who maintained unassisted breathing for at least two consecutive calendar days. If a patient survived for more than 48 consecutive hours of unassisted breathing but required assisted breathing (for any reason) before day 28, the number of VFD is the number of days of successful unassisted breathing through day 28. All periods of successful unassisted breathing (> 48 consecutive hours) are taken into account. Unassisted breathing is defined as being extubated with face mask, with nasal prong oxygen or room air or T-tube breathing or tracheostomy mask breathing or CPAP breathing with ≤ 8 cm H_2_O pressure support of assisted ventilator support, according to weaning protocol. Patients who die before day 28 will be assigned the number of days of successful unassisted breathing. If a patient required more than 28 days of mechanical ventilation, the value for VFD will be set to 0.

The parameter of ventilator-free days will be analyzed by means of an analysis of variance (ANOVA) model with treatment cohort as an independent class variable. Mean estimates will be provided, together with their corresponding two-sided 95% confidence intervals.

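### Baseline SOFA is collected but enters neither comparative efficacy model, and the VFD model has no baseline covariate at all: a loss of precision and robustness, not of validity

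*Protocol article*

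**What the plan says.** Two efficacy endpoints are given a comparative model in the protocol article.

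- **VFD** (Ventilator-free days (VFD) through day 28) is analysed "by means of an analysis of variance (ANOVA) model with treatment cohort as an independent class variable". Cohort is the only term. Patients who die before day 28 keep whatever days of successful unassisted breathing they had reached.
- **EVLWI** (Change from baseline to day 7 in EVLWI) is analysed by ANCOVA with the baseline EVLWI value and treatment cohort.

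On allocation, the section on sequence generation says: "No stratification factors are planned".

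Baseline SOFA is available, because the SOFA section says: "The absolute value and the change from baseline will be analyzed for SOFA score".

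The background on ARDS lists multiorgan dysfunction among the risk factors for mortality and attributes most ARDS-related deaths to multiorgan failure.

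The section on methods for additional analyses leaves subgroup analyses to the SAP. The covariates of the two models above are stated in the protocol itself.

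**The concern.** Organ-failure severity at entry is, on the protocol's own account, prognostic for death. Death caps the VFD a patient can accumulate, so severity should carry information about VFD as well. A VFD model with cohort alone leaves that information unused and puts it all into the residual variance. It also gives no correction if one cohort happens to start sicker, which unstratified allocation in active cohorts of 20 does not prevent.

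The same applies to EVLWI with less force: that model already has its own baseline value, and the document does not say how far SOFA predicts EVLWI change beyond it.

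The 125 mg contrast also decides whether the lower doses are compared with placebo at all, for both endpoints. The secondary objective is to review endpoints for a pivotal trial, so the precision and readability of these estimates matter even though efficacy is preliminary here.

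**Working it through.** **Inputs from the document** (Sample size): "a sample size of 20 evaluable patients in each treatment group will have approximately 80% power"; a "difference in means between solnatide and placebo of 3.2 ml/kg"; "with a common SD of 3.5"; "0.05 two-sided significance level and no alpha level adjustment for multiple testing". Placebo total: 35 in Trial design (10 + 5 + 20). The sequence-generation section gives 4:1 for the third step, where Trial design gives 1:1. At 4:1, 20 active patients imply 5 placebo patients, so 10 + 5 + 5 = 20 in total. Both sizes are carried through.

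**Assumptions, because the document gives no figure:** the share of patients with SOFA above 10 (30% to 50%), and the correlation ρ of baseline SOFA with EVLWI change beyond baseline EVLWI (0.2 to 0.5, so ρ² = 4% to 25%).

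**Step 1. The plan's own power.** Two-sample t-test, noncentral t:
- 20 vs 20: noncentrality = 3.2 / (3.5 × √(1/20 + 1/20)) = 2.89 on 38 df, power 80.4%. The stated figure of about 80% reproduces.
- 20 vs 35: noncentrality = 3.2 / (3.5 × √(1/20 + 1/35)) = 3.26 on 53 df, power 89.3%.

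**Step 2. Power with SOFA in the EVLWI model.** Residual SD = 3.5 × √(1 − ρ²), taking 3.5 as the SD before SOFA is added and ignoring the one df spent.

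| ρ | ρ² | Residual SD | Power 20 vs 20 | Power 20 vs 35 |
|---|---|---|---|---|
| 0 | 0% | 3.500 | 80.4% | 89.3% |
| 0.2 | 4% | 3.429 | 82.0% | 90.5% |
| 0.3 | 9% | 3.339 | 84.0% | 91.9% |
| 0.4 | 16% | 3.208 | 86.7% | 93.7% |
| 0.5 | 25% | 3.031 | 90.2% | 95.9% |

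The gain equals a sample-size factor of 1/(1 − ρ²), from 1.04 to 1.33.

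**Step 3. Chance imbalance in the share with SOFA above 10.** Exact calculation from two independent binomials with common prevalence p.

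| p | ≥20 points, 20 vs 20 | ≥20 points, 20 vs 35 | ≥30 points, 20 vs 20 | ≥30 points, 20 vs 35 |
|---|---|---|---|---|
| 30% | 22.6% | 12.6% | 5.6% | 2.1% |
| 40% | 25.8% | 15.3% | 7.5% | 3.0% |
| 50% | 26.8% | 16.2% | 8.1% | 3.5% |

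**Step 4. Validity.** Simulation under no treatment effect, with a normal outcome, ρ = 0.4 and 40,000 replicates. Overall type I error of the unadjusted test is 5.1% (20 vs 20) and 5.0% (20 vs 35). Among the trials with a mean SOFA difference above 0.5 SD (11% and 7% of trials by the normal calculation), it is 10.5% and 12.1% unadjusted, and 4.7% and 5.8% with SOFA in the model. The conditional excess is already averaged into the overall 5%.

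**Step 5. VFD.** The document gives no planning difference, SD or correlation for VFD, so no power gain can be computed for it. Step 3 does not depend on the endpoint and applies as it stands.

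**The case against.** The strongest reply is that nothing here is invalid. An unadjusted comparison of randomised groups holds its 5% level, as Step 4 shows. Efficacy is secondary and preliminary, the sample size rests on feasibility, and baseline characteristics will be tabulated by cohort. All of this stands. It limits the point to precision and robustness.

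The sizes also rest on assumptions. Only the variance that SOFA explains beyond baseline EVLWI counts, and with 35 placebo patients both the imbalance risk and the power shortfall are smaller. That stands too, and is why both placebo sizes are shown.

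One may ask why SOFA, when APACHE II, SAPS 3 and GOCA are also scored. SOFA measures organ failure directly, which is the risk factor that the protocol names, and its baseline value is already needed for a planned summary.

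Two stronger readings are tempting and not supported:

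- **That the Phase IIa result shows SOFA to be a driver of both outcomes.** The clinical-studies section calls the EVLWI effect "significant and more pronounced in patients with an initial Sequential Organ Failure Assessment (SOFA) score above 10" (P = 0.04) and the ventilation benefit more pronounced in the same subgroup (P = 0.06). These are exploratory subgroup contrasts of solnatide with placebo in a 40-patient study. They suggest possible effect modification, which a SOFA main effect does not capture, and they do not show how well SOFA predicts either outcome. Nor is a SOFA subgroup analysis missing: subgroup analyses are left to the SAP.
- **That SOFA adjustment would deal with differences between the sequential dosing steps.** It could address only the part of any drift that SOFA measures. The use of placebo patients from other steps is a separate question.

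**Conclusion.** The point holds as a worthwhile improvement, mainly for VFD, where a stated model omits every baseline covariate although a prognostic one is collected. The ground is the protocol's statement that multiorgan dysfunction predicts death, together with a VFD definition in which death ends the accrual of days. For EVLWI the case is weaker, because the named link is to mortality.

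An imbalance of 20 points or more in the SOFA above 10 share is not rare: about one chance in four at 20 vs 20 and about one in seven at 20 vs 35, for an assumed prevalence of 30% to 50%. The EVLWI power gain is about 2 to 10 percentage points at 20 vs 20 and 1 to 7 at 20 vs 35, for an assumed 4% to 25% of variance explained beyond baseline EVLWI. A reader might infer a similar gain for VFD, but the document gives no figures from which to derive one.

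**What to change.** Prespecify baseline SOFA total score, as a continuous covariate, in the VFD model as the priority, and add it beside baseline EVLWI in the EVLWI ANCOVA. Fix this in writing before unblinding, because a covariate added after an imbalance has been seen is not credible. Define the baseline measurement and say how a missing baseline SOFA is handled, so that the adjusted models do not drop patients. The unadjusted analyses can stay as sensitivity analyses.

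The cost is a few lines of text and one degree of freedom per model, with no new data.

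Separately, reconcile the third-step allocation ratio between Trial design and the sequence-generation section, since it determines which placebo size, and so which of the figures above, applies.

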## Statistical methods

### Statistical methods for primary and secondary outcomes {20a}

Data collected in this study will be listed and summarized as described below by treatment group. Data from all sites will be pooled and summarized. Continuous data will be summarized by mean, standard deviation (SD), median, first and third quartiles, minimum, and maximum. Categorical data will be presented by absolute and relative frequencies (n and %) or contingency tables. All statistical tables, listings, figures, and analyses will be performed by means of SAS® release 9.4 or later (SAS Institute, Inc., Cary, NC, USA).

A two-sided alpha level 0.05 will be considered. No alpha level adjustment will be made for secondary preliminary efficacy outcome variables and for multiple comparisons. Patients will be included in each analysis based on available assessments. No methodology for missing data handling will be applied, except for the EVLWI efficacy endpoint. Censoring rules for time-to-event analyses will be detailed in the Statistical Analysis Plan.

There is no primary efficacy endpoint as the primary objective of the study is to investigate the safety of solnatide. All efficacy analysis will be considered as secondary preliminary efficacy analyses. All secondary preliminary efficacy analyses will be performed based on the ITT set as primary analysis and on the PP set as supportive analysis and will be reported by planned treatment cohort.

No methodology for missing data handling will be applied for secondary preliminary efficacy endpoints, except for EVLWI. The homogeneity of treatment effects across different centers will not be tested.

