No multiplicity adjustment for multiple comparison will be applied, given that statistical comparison will be performed only between the highest solnatide dose cohort and the placebo cohort. A statistical comparison between lower dose(s) and placebo will be performed only in case of statistical significance of the comparison between the highest solnatide dose cohort and the placebo cohort.

#### Days of hospitalization through day 28

Length of hospital stay (in days) is defined as the difference between the discharge date and the randomization date. Patients still in the hospital at day 28 or who die during hospitalization will be censored at day 28. Days of outpatient hospitalization will not be included. Summary descriptive statistics will be provided for the number of days of hospitalization.

#### Days of stay at ICU through day 28

Length of stay at ICU (in days) is defined as the number of calendar days a patient was in the ICU. Patients still in the ICU at day 28 or who die during the stay at ICU will be censored at day 28. Summary descriptive statistics will be provided for the number of days of stay at the ICU.
2.Safety analyses

Safety analyses will be conducted on the Safety Set and will be reported by actual treatment cohort. No methodology for missing data handling will be applied for safety parameters.

#### Drug-related adverse events through day 14

The incidence of treatment-emergent drug-related AEs through day 14 after randomization, both in terms of number of events and in terms of patients with at least one event, will be tabulated by MedDRA System Organ Class (SOC) and Preferred Term (PT).

#### All adverse events through day 28

According to the onset date of the event, AEs will be defined as follows:
Treatment-emergent AEs are those events with an onset date after treatment initiation;Non-treatment-emergent AEs are those events with an onset date between screening and treatment initiation.

Non-treatment-emergent adverse events will be listed only. The incidence of treatment-emergent adverse events (TEAE) will be tabulated by MedDRA System Organ Class (SOC) and Preferred Term (PT). The incidence of TEAEs will also be summarized by system organ class, preferred term, and severity (based on investigator’s judgment).

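### Deaths held at day 28 and then summarised descriptively mix mortality with stay in the mean and SD of ICU and hospital days, and ICU stay has no start point

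*Protocol article*

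**What the plan says.** All the text at issue is in the Protocol article under Statistical methods {20a}.

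- **ICU stay.** The outcome is defined by time actually spent: "Length of stay at ICU (in days) is defined as the number of calendar days a patient was in the ICU". Deaths are then handled by a different rule: "Patients still in the ICU at day 28 or who die during the stay at ICU will be censored at day 28". The analysis is: "Summary descriptive statistics will be provided for the number of days of stay at the ICU".
- **Hospital stay.** It runs from randomization to discharge. For deaths: "Patients still in the hospital at day 28 or who die during hospitalization will be censored at day 28". The analysis is: "Summary descriptive statistics will be provided for the number of days of hospitalization".
- **Time to extubation.** It runs from randomization to first extubation. For deaths: "Patients still intubated at day 28 or who die while still intubated will be censored at day 28". The analysis is: "Summary descriptive statistics will be provided for the time to extubation".

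The opening of the same section says what descriptive statistics means here: "Continuous data will be summarized by mean, standard deviation (SD), median, first and third quartiles, minimum, and maximum". It also says that the SAP will set out the censoring rules for time-to-event analyses. A Kaplan-Meier summary is named for all-cause death only.

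Under Outcomes {12}, ICU days and hospital days are among the candidate endpoints for a future Phase III trial. Reviewing such candidates is the secondary objective under Objectives {7}.

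**The concern.** The protocol pairs a censoring rule with statistics that cannot use censoring. A mean and SD need a number for every patient, and the only number the text offers for a death in the ICU or hospital is 28. A patient who dies on ICU day 3 would then be tabulated with the longest stay the scale allows.

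Two things are at stake. First, the mean and SD of ICU and hospital days are natural inputs for choosing and sizing a Phase III endpoint, and here they would combine length of stay with mortality. Second, a cohort with more deaths would show a longer mean stay even if the other patients left at the same pace.

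Separately, ICU stay is given no start point and counts calendar days, whereas hospital stay is a date difference from randomization. The two columns would not be on the same scale.

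**Working it through.** The protocol gives no figure for these three outcomes, so there is none to reproduce. The size has to come from a formula and stated assumptions.

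**Inputs**

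- Value given to a death in that state: 28 (protocol).
- m, the share dying in that state by day 28: not given. I use 20% as an assumption, and 40.3%, which the Background section quotes as hospital mortality in moderate ARDS. The latter is not 28-day in-ICU mortality.
- t, mean day of death: not given; assumed 7 to 14.
- s, mean stay of all other patients: not given; assumed 12 to 21 days.
- SD of stay in those patients: not given; assumed 6 to 8 days.

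**Excess of the tabulated mean over days actually spent**

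Tabulated mean = m × 28 + (1 − m) × s. Mean of actual days = m × t + (1 − m) × s. The difference is m × (28 − t), so s drops out.

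- m = 0.20: 0.20 × (28 − 14) = 2.8 days; 0.20 × (28 − 7) = 4.2 days.
- m = 0.403: 0.403 × 14 = 5.6 days; 0.403 × 21 = 8.5 days.

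A check that needs no mortality rate: one death on day 3 in a cohort of 20 raises that cohort's mean by (28 − 3)/20 = 1.25 days.

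**Effect of a mortality difference alone**

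If mortality differs by 10 points and s is the same in both cohorts, the means differ by 0.10 × (28 − s): 0.10 × (28 − 21) = 0.7 days to 0.10 × (28 − 12) = 1.6 days.

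**Effect on the SD**

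Variance = (1 − m) × SD² + m × (1 − m) × (28 − s)². The second term exists only because deaths sit at 28. With m = 0.20, s = 15 and SD = 6: 0.8 × 36 = 28.8, and 0.16 × 169 = 27.0. The second term is 27.0/55.8 = 48% of the variance. Over the assumed ranges at m = 0.20 it runs from 13% (s = 21, SD 8) to 59% (s = 12, SD 6).

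**Median**

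Take an outcome timed from randomization, with no loss to follow-up before day 28. With deaths at 28, the share of patients with a value at or below any earlier day equals the cumulative incidence of extubation or discharge alive, with death as the competing event. A median below 28 is therefore the median of that curve, and a median of 28 means it was not reached. This covers time to extubation and hospital stay. It does not cover ICU stay as written, because its clock is not fixed.

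**ICU against hospital days**

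Inclusion requires ICU admission and at least 8 hours of stable ventilation, so some ICU time precedes randomization. Suppose a patient enters the ICU two days before randomization (day 0) and leaves both ICU and hospital on day 10. ICU calendar days run from day −2 to day 10, which is 13. Hospital stay is 10 − 0 = 10. Even counting ICU days from randomization, calendar counting gives 11 against 10.

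**The case against.** The strongest reply is that the protocol says censored, not assigned the value 28, and leaves censoring rules for time-to-event analyses to an SAP that is not shown. Entry as a plain value is indeed an inference. It is still the natural reading, because the article states the censoring rule itself and names only descriptive statistics beside it. The other readings do not rescue the mean: dropping deaths leaves a selected group, and treating 28 as truly censored makes a plain mean and SD invalid.

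A reader might infer that these tables would largely reflect mortality. The documents do not support that. They give neither 28-day mortality in the ICU or hospital nor survivor stay, and the eligibility criteria exclude several groups with a very poor outlook. Under the assumed s of 12 to 21 days, deaths supply 25% of the tabulated mean at m = 20% and s = 21 (5.6 of 22.4 days), and 61% at m = 40.3% and s = 12 (11.3 of 18.4 days). That is a minority in one case and a majority in the other.

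A reader might also infer that time to extubation is overstated. That does not follow, since a patient who dies intubated has no true extubation time to overstate. Holding such deaths at day 28 is a usual device for cumulative incidence, and it stops an early death from looking like a quick success.

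The other side is also right that the median survives for outcomes timed from randomization, that deaths are reported by cohort as counts, proportions and Kaplan-Meier curves, and that none of these three outcomes is tested. Ventilator-free days, the duration outcome that is tested, credits deaths with the unassisted days they achieved.

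**Conclusion.** The point holds for the mean and SD of ICU stay and hospital stay, on the natural reading and unless the SAP provides otherwise. For ICU stay the death rule also contradicts the stated definition. Hospital stay has no such literal clash, because it is defined by a discharge date that a patient who dies does not have. For time to extubation only the mean and SD are unsuitable.

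The excess over days actually spent is 2.8 to 4.2 days at m = 20%, and 5.6 to 8.5 days if m were as high as the background hospital figure of 40.3%. Both ranges rest on an assumed mean day of death of 7 to 14. The missing ICU start point and the differing day counts are a definite fault in the text, whatever the mortality.

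The weight is modest: the outcomes are secondary, descriptive and untested, and a reader can see the deaths elsewhere. It merits correction because ICU and hospital days are listed Phase III candidates, and their means and SDs would be carried forward.

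**What to change.** - Summarise extubation, ICU discharge alive and hospital discharge alive, each from randomization, by cumulative incidence with death as the competing event and administrative censoring at day 28. Report by cohort the day-28 proportion with its 95% confidence interval, and the median where it is reached.
- If mean days are tabulated, use actual days and show survivors and deceased patients separately.
- Count ICU days from randomization with the same day-count rule as hospital stay.
- If the SAP already does this, bring the protocol wording into line with it.

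The cost is a few sentences and a standard analysis of data already collected, with no change to design, sample size or visits. The small downside is that a cumulative incidence is a less familiar summary than a mean number of days.

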The same analysis will be repeated for SAEs regardless of drug relationship, for drug-related SAEs, AEs with an outcome of death, and AEs leading to discontinuation of treatment. Deaths reportable as SAEs will be listed by patient and tabulated by MedDRA SOC and PT.

#### All-cause deaths through day 28

The number and proportion of deceased patients will be reported. In addition, the time (in days) from randomization to the event will be used for analysis. Subjects without an event will be censored at the earlier of the last contact date or day 28. The Kaplan-Meier estimates of the survival functions for each treatment cohort will be plotted and summarized.

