### Adverse event reporting and harms {22}

All identified non-serious AEs (related and unrelated) must be recorded and described on the non-serious AE page of the eCRF.

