#### Serious adverse event reporting

Every SAE, regardless of suspected causality, occurring after screening and until at least 28 days after randomization must be reported to the sponsor within 24 h of site awareness. Any SAE experienced after this 28-day period should only be reported to the sponsor if the investigator suspects a causal relationship to the study treatment. Recurrent episodes, complications, or progression of the initial SAE must be reported as follow-up to the original episode within 24 h of the investigator receiving the follow-up information. Information about all SAEs will be recorded on the AE page of the eCRF and transmitted through the SAE tool. In case of technical difficulties, SAE notification can be carried out by sending a paper SAE form to the Pharmacovigilance Officer via email or by fax.

All SAEs still ongoing at end of study will be followed up by means of queries requesting updates. Other supporting documentation of the event may be requested by the study sponsor and should be provided as soon as possible. The study sponsor will be responsible for notifying Health Authorities of any unexpected fatal or life-threatening suspected adverse reaction as soon as possible, but in no case later than 7 calendar days after the sponsor’s initial receipt of the information.

Suspected unexpected serious adverse reactions (SUSARs) will be collected and reported to the competent authorities and relevant ethics committees in accordance with Directive 2001/20/EC or as per national regulatory requirements in participating countries.

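### Drug-related adverse events are tabulated only to day 14, while all adverse events and drug-related SAEs run to day 28, so late non-serious related events enter no drug-related table and the two drug-related tables cannot be reconciled

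*Protocol article*

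**What the plan says.** All of this comes from the protocol article; the SAP is not at hand.

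- **Drug-related AEs.** Statistical methods {20a}, safety analyses, *Drug-related adverse events through day 14*: "The incidence of treatment-emergent drug-related AEs through day 14 after randomization" is tabulated by MedDRA SOC and PT, as a count of events and as a count of patients.
- **All AEs.** The next heading is "All adverse events through day 28". It defines the term without an end day: "Treatment-emergent AEs are those events with an onset date after treatment initiation". TEAEs are tabulated by SOC and PT, and "The incidence of TEAEs will also be summarized by system organ class, preferred term, and severity". No split by drug relationship is given.
- **Repeats under the day-28 heading.** "The same analysis will be repeated for SAEs regardless of drug relationship, for drug-related SAEs, AEs with an outcome of death", and also for AEs that lead to discontinuation of treatment. Drug-related AEs overall are not on this list.
- **Recording.** Item {22}, on harms, states the rule for sites: "All identified non-serious AEs (related and unrelated) must be recorded and described on the non-serious AE page of the eCRF". Under *Serious adverse event reporting*, SAEs "occurring after screening and until at least 28 days after randomization must be reported to the sponsor within 24 h of site awareness". After that period an SAE is still reportable if the investigator suspects a causal link.
- **Duration.** Trial design {8}: up to 7 days of treatment and up to 28 days of study per patient.

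**The concern.** The day-14 window is a rule that the article states, not a detail it leaves open. The rule sits badly with its neighbours. The protocol takes late causality seriously enough to tabulate drug-related SAEs under the day-28 heading and to keep collecting suspected related SAEs beyond day 28. For non-serious events it asks sites to record related and unrelated events alike. The table that sums up relatedness nevertheless closes at day 14.

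Safety is the main objective and each dose group has 20 patients, so a few events visibly move a tabulated incidence. What is at stake is whether the drug-related output is complete and internally consistent. No test, sample size or error rate is affected.

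**Working it through.** The article gives no figure to reproduce here. The check compares windows and adds day arithmetic.

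**1. Windows side by side**

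| Output | Stated window | Relationship shown? |
|---|---|---|
| Drug-related TEAEs (SOC/PT) | to day 14 | yes |
| All TEAEs (SOC/PT; also by severity) | day-28 heading | no |
| All SAEs | day-28 heading | no |
| Drug-related SAEs | day-28 heading | yes |
| Fatal AEs; AEs leading to discontinuation | day-28 heading | no |

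**2. Follow a non-serious event with onset on day 18, judged drug-related, that neither is fatal nor stops treatment.** It is treatment-emergent, so it enters the all-TEAE tables. It is not an SAE, so it is in neither SAE table. It falls after day 14, so it is not in the drug-related AE table. It appears in no drug-related table.

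**3. Follow a drug-related SAE with onset on day 20.** It enters the drug-related SAE table but not the drug-related AE table. In a cohort where this is the only drug-related event, the drug-related AE table shows 0 and the drug-related SAE table shows 1. The implied number of non-serious related events is 0 − 1 = −1. The subset can therefore exceed its parent, and non-serious related events cannot be obtained by subtraction.

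**4. Length of the uncovered window**

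- Share of the study period: (28 − 14) / 28 = 14/28 = 50%.
- Share of the time after the 7 treatment days: days 8 to 28 are 28 − 7 = 21 days, and 14/21 = 67%.

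These are calendar shares. They would be shares of events only if related events were equally likely on every day, and nothing in the document supports that.

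**5. Illustration under assumed rates.** The document gives no rate for late, non-serious, related events. Let p be the assumed proportion of solnatide patients with at least one. The chance that a 20-patient dose group contains an affected patient is 1 − (1 − p)^20. The expected number among 3 × 20 = 60 solnatide patients is 60p.

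| Assumed p | Chance of at least one in 20 | Expected among 60 |
|---|---|---|
| 2% | 33% | 1.2 |
| 5% | 64% | 3.0 |
| 10% | 88% | 6.0 |

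The true rate may lie below this range. The table shows only how p translates into patients absent from the drug-related table.

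**The case against.** **The two analyses simply have different, stated windows.** A table labelled day 14 is not wrong about day 14. The same cut is used for vital signs, laboratory values, ventilation parameters and driving pressure, so it looks deliberate: seven treatment days plus seven. This stands as an explanation. It does not settle the matter, because AEs are analysed to day 28, and it does not repair the mismatch with the drug-related SAE table.

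**A shorter attribution window is arguable on pharmacology.** The pre-clinical background reports rapid clearance from blood in animals and no drug found in rat lung about 30 to 90 minutes after treatment ended. *Known potential risks* reports very low and brief plasma levels. This stands, and it suggests few late related events. But the article does not offer it as the reason for day 14, and the drug-related SAE analysis does not follow that logic.

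**The events are not lost.** This stands. They remain in the all-TEAE tables, and listings may well show relationship, since the article says collected data will be listed as well as summarised. What is missing is the tabulation by relationship.

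**A fuller set of tables may be in the SAP.** That is possible. The point is limited to what the article itself fixes.

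**Day 28 for non-serious AEs is partly inferred.** It comes from the analysis heading; the reporting section gives no end day for non-serious AEs. This stands as a limit.

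**Stronger readings that the document does not support.** A reader might infer that the trial's main safety answer is biased downward. Outcomes {12} and the DSMB section rest safety on mortality, AE and SAE incidence, laboratory data and ECG, not on drug-related AEs. A reader might also infer that the DSMB decides on truncated data. Trial design {8} has it review safety data from the 28-day period before the first escalation, and nothing confines it to the day-14 table. Finally, the 50% and 67% might be read as shares of drug-related events missed, which they are not.

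**Conclusion.** The point holds in a limited form. As written, a non-serious event judged drug-related with onset on days 15 to 28 enters no planned drug-related table, and the drug-related AE and SAE tables cannot be reconciled because the subset has the longer window.

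The size is a window of 14 days out of 28. The number of events in it cannot be derived from the document and may be small. The conclusion assumes that the day-28 heading governs both the TEAE tables and their repeats, and that the investigator's judgement of relationship is recorded for non-serious events, as the reporting section implies.

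This is a modest defect in how a safety output is specified. It is worth correcting because safety is the main objective and the correction is nearly free.

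**What to change.** - Add drug-related AEs to the list of analyses repeated under the day-28 heading, so that treatment-emergent drug-related AEs are tabulated by SOC and PT through day 28, as events and as patients with at least one event.
- Keep day 14 as a split within that table: onset to day 14, and onset on days 15 to 28. The window already planned stays visible, and the drug-related SAE table becomes a true subset.

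The cost is one descriptive table from onset and relationship data already recorded. Sample size, power and alpha do not change. The reported drug-related incidence may be slightly higher than under the day-14 cut.
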